Importantly, self-reported outcome measures are underrepresented in meta-analyses comparing LHB tenodesis and tenotomy. While clinical outcomes assessed by a clinician provide valuable information on recovery after surgery, the patient’s perspective may be even more important. Often, clinician-reported and patient-reported outcomes will correlate, but this is not always the case. For instance, a Popeye deformity reported by a clinician may not be noticed by patients, and often does not bother them [8]. To determine the clinical relevance of previously reported findings, it is critical to consider both patient’s and the clinician’s perspectives. In other words, clinical measures (e.g. range of motion, strength, MRI) should be complemented with patient-reported outcomes (e.g. self-reported function, pain, cosmetic appearance, and quality of life).

Therefore, we designed this multicenter, prospective randomized controlled trial that aims to compare the functional results between LHB tenotomy and LHB tenodesis when performed during arthroscopic rotator cuff repair. The primary outcome measure of this trial is the Constant Score at 1 year follow-up. Secondary objectives are to compare elbow flexion strength, Popeye deformity, and patient reported function and quality of life between intervention groups. In addition, we aim to quantify the relation between clinician-reported and patient-reported function and cosmetic appearance (Popeye phenomenon) in our population. Based on the largest meta-analysis so far [7], we hypothesize no difference in functional outcome after tenotomy compared to tenodesis, as reflected in similar Constant scores at 1 year follow up.

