### Outcome measures

#### Primary outcome

The primary outcome measure is the Constant score at 1 year follow up.

The Constant score is a 100 points scale consisting of four variables, which includes a patient reported part (pain 15 points and activity level 20 points), which results in a total of 35 points. Next to this there is a physician rated part (shoulder strength 25 points and range of motion 40 points) which totals 65 points [18]. As scores of the Constant-Murley test are gender related and will decrease with age, we will normalize the summed scores according to Katolik et al. [19].

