### Statistical analysis

Statistical analyses will be done using the Statistical Package for the Social Sciences (SPSS Chicago, Illinois, USA). Analyses will be performed according to the intention to treat principle. To test our main hypothesis that LHB tenodesis and tenotomy result in similar functional outcome at 1 year follow up, Constant scores will be compared between groups using an independent samples t-test. In the unlikely event that a baseline difference is observed between groups, the change in Constant score from baseline to 1 year post-surgery will be used for analysis. Given the non-inferiority design, a one-sided *P*-value <0.025 will be considered statistically significant. Statistical uncertainties will be quantified using 95 % two-sided confidence intervals.

To further compare recovery after the two surgical interventions, longitudinal data analysis (mixed model or generalized estimating equations (GEE)) [28] will be used. In the primary model, the Constant score will be included as the dependent variable, and treatment allocation (between subjects) and time (within subjects) will be included as the key independent variables. Other variables that may affect outcome (e.g. age, center of inclusion) will be included as covariates. The interaction between group and time will be assessed to evaluate whether the two treatment groups differed in change over time. The secondary outcome variables (e.g. shoulder function on the DASH and OSS, quality of life on the EQ5D, pain on the VAS, Elbow strength, MRI findings, and cosmetic appearance) will be analyzed in using similar models. For all longitudinal data analysis analyses, a two-tailed value of *p* < 0.05 is considered statistically significant.

To evaluate the relation between patient-reported and clinical measures of function, we will calculate correlation coefficients for continuous outcome measures (e.g. DASH and OSS questionnaires versus Constant scores and elbow flexion strength). To assess agreement between the presence of a Popeye deformity (y/n) as reported by the patient, clinician, independent observers, and based on MRI, we will calculate Kappa coefficients.

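### For the aim of relating clinician-rated to patient-reported function, the plan correlates DASH and OSS with a Constant score that is 35% patient-reported, so the relation will very likely be overstated

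*Protocol article*

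**What the plan says.** The last paragraph of the Background sets an additional aim: "we aim to quantify the relation between clinician-reported and patient-reported function and cosmetic appearance (Popeye phenomenon) in our population". Earlier in the same section, range of motion, strength and MRI are given as examples of clinical measures, and self-reported function and pain as examples of patient-reported outcomes.

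The Statistical analysis section carries out the function part of this aim: "To evaluate the relation between patient-reported and clinical measures of function, we will calculate correlation coefficients for continuous outcome measures". The pairs given as examples are "DASH and OSS questionnaires versus Constant scores and elbow flexion strength".

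The Primary outcome section describes the Constant score as a mixture. It has a "patient reported part (pain 15 points and activity level 20 points), which results in a total of 35 points" and a "physician rated part (shoulder strength 25 points and range of motion 40 points) which totals 65 points". Of its analysis form it says only that "we will normalize the summed scores", for age and sex. Table 1 lists the score as the main outcome measure, under neither the patient-reported nor the clinician-reported heading.

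**The concern.** The correlation is meant to set the patient's view of function against the clinician's. DASH and OSS stand on the patient's side. The Constant score is placed on the clinical side, although about a third of its points are the patient's own rating of pain and activity. By the Background's own sorting, those points belong with DASH and OSS.

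The overlap is in content as well as in source. Under PROMs, DASH is described as covering physical function and symptoms, and OSS as covering shoulder complaints. The pain and activity items of the Constant score cover similar ground and are answered by the same patient.

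At stake is the reading of a secondary result. The Background argues that clinician and patient reports do not always correspond. A coefficient that contains patient report on both sides tends to hide the divergence that the aim is meant to show.

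**Working it through.** **1. Composition of the score (Primary outcome section).** Patient-reported: 15 + 20 = 35. Physician-rated: 25 + 40 = 65. Total: 35 + 65 = 100. The stated split is reproduced.

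**2. Formula.** Let s_p and s_c be the SDs of the patient-reported and physician-rated parts, r_pc the correlation between the parts, and r_p and r_c the absolute correlations of DASH (or OSS) with each part. The sign is reversed for DASH, where a higher score means more disability. For the summed score:

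r_total = (s_p·r_p + s_c·r_c) / √(s_p² + s_c² + 2·r_pc·s_p·s_c)

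The article gives none of these five inputs, so all are assumptions. The formula applies to the raw sum. Normalising for age and sex would change the figures somewhat but does not remove the patient-reported items.

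**3. Illustration.** Take s_p = 7, s_c = 11, r_pc = 0.4, r_p = 0.7, r_c = 0.3.

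- Numerator: 7 × 0.7 + 11 × 0.3 = 4.9 + 3.3 = 8.2
- Denominator: √(49 + 121 + 2 × 0.4 × 77) = √231.6 = 15.22
- r_total = 8.2 / 15.22 = 0.54, against r_c = 0.30

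The implied SD of the total, 15.2, is close to the 16 points used in the Sample size section, so the assumed SDs are reasonable.

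**4. Sensitivity to r_c, other inputs unchanged.**

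| r_c (physician-rated part) | r_total |
|---|---|
| 0.2 | (4.9 + 2.2) / 15.22 = 0.47 |
| 0.3 | 0.54 |
| 0.4 | (4.9 + 4.4) / 15.22 = 0.61 |

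**5. When the total exceeds the physician part.** Setting r_total > r_c gives r_p / r_c > (15.22 − 11) / 7 = 0.60. DASH need not follow the patient part more closely than the physician part for the total to be raised.

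**6. Wider grid.** The inputs were r_p 0.5, 0.6, 0.7, 0.8; r_c 0.3, 0.4, 0.5, 0.6; r_pc 0.3, 0.5, 0.7; SD ratio 35:65 or 1:1. This makes 4 × 4 × 3 × 2 = 96 cases. The total exceeded the physician part in 95.

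- Largest excess: +0.38 (r_p 0.8, r_c 0.3, r_pc 0.3, equal SDs: 1.1/√2.6 = 0.68 against 0.30).
- The exception: −0.003 (r_p 0.5, r_c 0.6, r_pc 0.7, equal SDs: 1.1/√3.4 = 0.597 against 0.60).

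**7. Limiting case.** If the physician-rated part had no relation to DASH/OSS or to the patient part (r_c = r_pc = 0), the total would still correlate 0.28 (r_p 0.6, SD ratio 35:65) to 0.57 (r_p 0.8, equal SDs).

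**The case against.** The pairs are introduced as examples, in a condensed article whose full protocol and SAP are not shown. Nothing rules out an additional analysis of the physician-rated part. That is true, but the Constant pairing is expressly named as a clinical measure of function, and the summed score is the only form defined. Followed as written, the overlap is there.

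Elbow flexion strength is also named. It is a dynamometer measure with no patient-reported content, so part of the aim is already met without overlap. This stands, and that pairing should stay. It measures elbow flexor power, however, and does not replace clinician-rated shoulder motion and strength.

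A reader might infer that the correlation is inflated by construction. The document does not support that. DASH and OSS are separate instruments and not components of the Constant score, so this is not a part-whole correlation in which inflation is automatic. The grid contains one case without it.

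A reader might also infer that clinician–patient agreement would be overstated. For function the plan computes correlations; it reserves agreement, measured by kappa, for the Popeye deformity. Nor is this aim a main reason for the trial: the Background adds it after the primary outcome and the listed secondary objectives.

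Finally, the correlation is descriptive, with no threshold attached, and the article discloses the mixed composition. That limits the consequence but does not make the coefficient answer the stated question.

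**Conclusion.** The point holds as a minor one. The DASH/OSS–Constant correlation mixes patient report with clinician rating on the side labelled clinical, and will very likely overstate the relation between clinician-rated and patient-reported function. The overlap is certain from the text. Its effect is very likely upward, but the size cannot be fixed from the document: 0.54 against 0.30 is an illustration that rests wholly on the assumed SDs and correlations.

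The stronger inference, that the trial's main result is compromised, is not supported. The primary non-inferiority comparison, the elbow flexion strength correlations and the Popeye kappa analyses do not depend on this choice.

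**What to change.** For this aim, correlate DASH and OSS with the 65-point physician-rated part of the Constant score (strength plus range of motion). Keep the planned pairing with elbow flexion strength. If the total-score correlation is also reported, label it as containing patient-reported pain and activity items. The article describes normalisation for the summed score only, so also state whether the 65-point part is used in raw points.

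The cost is one sentence in the analysis section and a few extra coefficients. The four components must be scored to form the total, so no new data, visits or patients are needed.

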## Discussion

With this multicentre, prospective patient blinded randomized level I study we will contribute to elucidating the controversy in the treatment of LHB tendon pathology in arthroscopic rotator cuff surgery. If our main outcome measure, the Constant score, is not lower in the group that underwent tenotomy, this increases the level of evidence to support previously reported findings that functional outcome is similar between treatments. Our thorough assessment of Popeye deformity (by the patient, the treating surgeon, and blinded assessors using digital pictures, complemented with MRI imaging) will reveal how this patient population values cosmetic appearance. While a Popeye deformity is more common after tenotomy, it is to date unknown to what extent this bothers patients older than 50 years.

A limitation of this study is that our comparison of costs is limited to the duration of surgery, without taking into account any other financial aspects. With regard to surgical material, no differences are expected, as tenodesis can be performed with the same anchor that is already used for the rotator cuff repair. One could speculate that tenotomy may allow for earlier return to work or activities, but this potential advantage would be masked by our study design as both groups received the same post-operative rehabilitation instructions.

The results of this study will strengthen the evidence on potential risks and benefits associated with tenotomy and tenodesis. Insight in the differences between treatment effects is very important, as managing patient expectations is critical in current orthopaedic practice.

## Abbreviations

ADL: Activities of daily living
BITE: BIceps tenotomy or tenodesis
DASH: Disabilities of the arm, shoulder and hand questionnaire
DOST: Dutch translation of Oxford shoulder test
EQ-5D: Euroqol-5 dimensions
GCP: Good clinical practice
GEE: General estimated equations
LHB: Long head biceps
METC: Medische ethische toetsings commissie
NVA: Nederlandse vereniging voor arthroscopie
OLVG: Onze lieve vrouwe gasthuis
RCT: Randomised controlled trial
VAS: Visual analogue scale
